### Setting

The study will take place in one region of Northern Ireland, the Northern Health and Social Care Trust, and in one region of London, Camden and Islington. We have chosen these sites to maximize recruitment across a large population and improve the applicability of our results. They cover a range of urban and semi-rural areas and include areas with high levels of deprivation (a lack of resources, opportunities and/or services) and where London’s population is ethnically and culturally diverse. We will use a range of mainstream community older persons’ groups to deliver the Matilda intervention accessed via Volunteer Now in Northern Ireland and the Camden & Islington Foundation Trust volunteer service in London.

To be involved in the study, the older person, mainstream community groups, and mentors at the clinical sites must be prepared to participate in the Matilda training and be prepared to support an older person with an intellectual disability in the group. They must also demonstrate and document a willingness to comply with the study protocol and applicable regulatory requirements, sponsor, and local policies.

### Participants — older adults with an intellectual disability

Older adults with an intellectual disability (≥45 years) living in the community will be assessed using the inclusion and exclusion criteria as set out below. According to the American Association on Intellectual and Developmental Disabilities (AAIDD), intellectual disability is characterized by significant limitations in both intellectual functioning (reasoning, learning, problem solving) and in adaptive behavior, which covers a range of everyday social and practical skills, and originates before the age of 18 [35]. Eligibility to participate in the trial will be confirmed by a health and social care provider.

### Inclusion criteria

Adults with an intellectual disability will be eligible to participate in the study in accordance with the following criteria:Mild/moderate intellectual disabilityLiving in the community with a family member(s) or in any type of community accommodation (residential/supported)  ≥45 yearsAble to communicate verbally andAble to provide informed consent.

### Exclusion criteria

Adults with an intellectual disability will be excluded to participate in the study in accordance with the following criteria:Severe/profound intellectual disabilityPresenting with severe challenging behaviourUnable to communicate verbally or in EnglishUnable to provide consent andAlready accessing mainstream community groups.

### Sample size

The chosen sample size is justified based on feasibility outcomes, specifically estimating the proportion of adults with intellectual disability who are recruited and retained. With 64 participants, if observed retention is 60%, the 95% CI for the true proportion retained would be approximately 46% to 71%.

### Participants and mentors

#### Screening and recruitment strategy

Posters and flyers will be used to recruit potential local community groups and mentors in each site. The campaign will be run by the mainstream Volunteer Now organisation in Northern Ireland and Camden & Islington Foundation Trust volunteer service in London. A Volunteer Co-ordinator will be appointed to each site and based in each of these organisations. The Volunteer Co-ordinator will provide information and awareness-raising sessions to those local community groups interested in the aim and purpose of the Matilda project; answering any questions the groups may have and meeting potential mentors. People interested in being mentors in the study will be asked to complete an application form to ensure they meet the inclusion criteria and attend an informal interview with the Volunteer Co-ordinator. When written consent has been obtained from those meeting the above criteria to participate in the study as a mentor, the research staff will arrange to undertake the baseline questionnaires within 2 weeks.

### Inclusion criteria

People will be eligible to participate in the study as a mentor in accordance with the following criteria:Attend a local community groupProvide written consentComplete registration and declaration of convictions forms

### Exclusion criteria

People will be excluded from participation in the study as a mentor in accordance with the following criteria:Have a criminal recordConsent declined

### Training mentors

Mentor training will be delivered by the Volunteer Co-ordinator in each site and will cover background to the Matilda project and the role of the mentor, disability awareness training, working with adults with intellectual disability, communication strategies, and safeguarding training (incl. confidentially, identifying signs of abuse, managing behaviours that challenge, lone working). This group training will last 3 h, and mentors will be provided with tea/coffee and lunch. The mentors will also receive monthly supervision from the Volunteer Co-ordinator in each site, either face-to-face, by telephone, or online to ensure the safety/wellbeing of the adult with an intellectual disability and check the fidelity of the intervention.

In Northern Ireland, we will work very closely with Volunteer Now. Volunteer Now is the lead organisation for promoting and supporting volunteering across Northern Ireland. It supports local community groups and voluntary organisations through the provision of training, promoting their volunteering opportunities, support with safeguarding, etc. Volunteer Now supports more than 40 mainstream older people community groups across Northern Ireland such as Men’s Shed, Knit and Knatter, recreational groups (i.e. bowling), etc. They have access to approximately 3000 older adults without an intellectual disability who are registered volunteers who could be potential mentors for the Matilda project. Volunteer Now will recruit the Volunteer Co-ordinator, identify, and recruit the local community groups and the mentors, and provide the training and supervision for the mentors for the course of the Matilda project. Volunteer Now will work closely with the research team and the Volunteer Co-ordinator in the Camden & Islington Foundation Trust Volunteer Service, London.

In London, we will work with the Camden & Islington Foundation Trust volunteer service who will advertise and recruit the Volunteer Co-ordinator, identify the local community groups and mentors, and provide the training and supervision of the mentors. Part of the Camden & Islington Foundation Trust Volunteer Service includes a section for Activity Support and Befriending Volunteers (Services for Ageing Mental Health). The leader of the Camden & Islington Foundation Trust Volunteer Service will work closely with Volunteer Now to ensure the uniformity of the training, monitoring, and supervisory arrangements across the two sites.

### Consent

Written informed consent must be obtained by the Research Associate (RA) on each site prior to the collection of trial data and the provision of the intervention. It must be assumed that an adult with an intellectual disability has the capacity until proven otherwise. Therefore, it is important that the person is given the information required in a user-friendly format to make an informed decision using reasonable adjustments. Managing on-going consent, including assessment of capacity to consent, will take place using the following steps.

Research Associates will undertake the Good Clinical Practice Course and receive specific training at each site in how to assess capacity to consent and ensure informed consent is maintained throughout the project on a case-by-case basis. All participants will receive an easy read Participant Information Sheet (PIS) and consent form with pictures or symbols to explain the purpose of the study and what is involved. The PIS and consent form have been prepared in collaboration with our PPI representatives. The RAs will clearly explain the decisions to be made about joining the Matilda Project, completing some questionnaires at several time points, being randomised to either the intervention or control arm, and taking part in the process evaluation interview (qualitative study) using the user-friendly PIS or additional media or communication aids if required. The Research Associates will explain what is involved in participating in the Matilda Intervention (joining a community group, being matched to two or three mentors within the group, time commitments) and being randomised to the control group. The Research Associates will assess if the person can retain the information and where appropriate have present a family member or advocate who is familiar with the communication needs of the person with the intellectual disability.

### Matilda intervention

The original TTR social intervention was established to explore the retirement options for older adults with an intellectual disability engaged in employment in Australia and to assess possible pathways to retirement [36]. The theoretical underpinnings of the TTR intervention are the Active Support Model [37] and the Co-Worker Training Model, where potential mentors are provided with training and then matched with an older adult with an intellectual disability to access a local community group: it is a peer-led intervention.

The TTR intervention has three components: (1) promoting the concept of retirement, (2) laying the groundwork for inclusion of would‐be retirees with an intellectual disability, and (3) constructing the reality. The third component comprises five stages: planning, locating a group, mapping new routine, recruiting and training mentors, and monitoring and ongoing support [37]. Adults with an intellectual disability reported increased social connectedness, less loneliness, improved wellbeing, and better quality of life after engaging in the TTR project. No data were collected on the benefits of the project for the mentors. In consultation, it was agreed that this intervention could be adapted to older people with an intellectual disability generally, regardless of employment status.

We adapted the TTR project to a UK context. We held 7 focus groups with senior staff from local disability and mainstream older person charities, potential mentors, older adults with an intellectual disability, and their carers. Three co-production workshops with key stakeholders explored how the TTR project could be adapted for a UK context. The key issues identified were agreement to give less emphasis to retirement, reflected in its new acronym ‘Matilda’.

### Matching of adults with an intellectual disability, mentors, and local community groups

The Volunteer Co-Ordinator and the disability staff in each site will meet with one older adult with an intellectual disability and their carers at a time, to explore the person’s needs, capabilities, interests, and hobbies, to identify a suitable local community group and discuss the logistics of attendance (availability of both the adult with the disability and the mentors, transportation to and from the community group, when and where the older adults and mentors would meet, etc.).

The Volunteer Co-ordinator will support the 1–2 mentors to facilitate the person with the intellectual disability to attend the local community group. This will continue until the mentors feel they are confident in supporting the adult with the intellectual disability, and the adult is comfortable with the arrangements. Support will be individually tailored, with the Volunteer Co-ordinator regularly following up to ensure that the adult with the intellectual disability is attending and actively involved in the community group (visits, phone, text). Mentors and carers will be able to contact the Volunteer Co-ordinator and intellectual disability staff for advice. By their nature, local community groups such as men’s sheds, sporting activities, knitting, or gardening groups vary in their frequency and duration, typically between 1 and 4 h over 1 to 3 sessions per week. The adult with the intellectual disability will be supported by their mentors to attend the group and facilitate their involvement with the group for 6 months.

### Control or comparator group

Participants randomised to the Matilda group will also receive usual care, ensuring that they do not lose any care that is standard. Those in the control group will receive usual care and will be offered three group recreational activities. Details regarding participants’ usual care will be confirmed at the start of the study and again at the end of the study. The participants in the control group will complete data gathering instruments at baseline, 6, and 12 months from consent being given.

### Outcome measures

#### Primary outcome measure

We will use both quantitative and qualitative methodologies to examine the feasibility outcomes of the Matilda intervention (i.e. assess eligibility, recruitment rates and pathways, consenting rate, randomisation process, matching of mentors (and local community groups) and older adults with an intellectual disability, training and supervision, attendance levels, dropout rates, and retention of participants).

#### Secondary outcome measures for adults with intellectual disability

These have been chosen based on the measures used in the original TTR project and our experience with older adults with intellectual disability. They reflect the total measurement load that adults with an intellectual disability have been willing to bear, and the need for brevity and good psychometric properties.Health-related QOL**:** WHOQOL-Dis is a measure of health-related quality of life developed by the WHO [38]. This 26-item short version consists of two benchmark items on general health (not used in the scoring) (one general QOL item, one general health item) and 24 specific items which generate a total score and four domains: physical health, psychological health, social relationships, and environmental QOL. Each item is answered on a 5-point Likert scale, which assesses the intensity, capacity, frequency, and evaluation of QOL facets with respect to the last 2 weeks. The WHOQOL-Dis has been validated in intellectual disability individuals. Anxiety: Glasgow Anxiety Scale for people with Intellectual Disability (GAS-ID) was developed for adults with an intellectual disability [39], which is a 27-item self-report scale. It has been used in several psycho-interventions for adults with an intellectual disability and found to have good psychometric properties. Scores range from 0 to 40, and higher scores indicate more symptoms.Loneliness and social satisfaction: The Modified Worker Loneliness Scale is a 12-item questionnaire that measures loneliness in adults with an intellectual disability. It has been used in several intellectual disability interventions and found to have good psychometric properties [40].WHO Wellbeing 5**:** A short 5-item scale to measure subjective wellbeing [38].Service use and costs: The study-specific Client Receipt Services Inventory [41] will be used to collate service use and costs for people with an intellectual disability over the 12 months of the study for the preceding 6 months at each follow-up point. It will be completed by the adult with an intellectual disability and their family/paid carer.EQ-5D-Y [42]: This questionnaire has simplified wording and has been used previously in adults with an intellectual disability (Jahoda et al., 2017). It is a generic preference-based measure of health-related quality of life, which provides a description of health using five dimensions (mobility, self-care, usual activities, pain/discomfort, and anxiety/depression), each with levels of severity.

#### Secondary outcome measures for mentors

Health Related Quality of Life: WHOQOL-Dis is a measure of quality of life developed by the WHO [43]. This 26-item short version consists of four domains (physical health, psychological health, social relationships, and environment QOL).Psychological well-being and quality of life: The Warwick Edinburgh mental wellbeing scale (WEMWBS) [44] is a 14-item questionnaire that measures psychological well-being and quality of life in the adult general population.Attitudes Towards People with an intellectual disability: The 67-item Attitudes Towards Intellectual Disability Questionnaire (cognitive, affective, and behavioural components) [45].EQ-5D-Y [46]: This is a generic preference-based measure of health-related quality of life, which provides a description of health using five dimensions (mobility, self-care, usual activities, pain/discomfort, and anxiety/depression), each with levels of severity.

As a token of gratitude and to encourage completion of the measures, the adults with an intellectual disability and their mentors will each be offered a financial incentive of a £10 voucher at each of the three time points. A £10 payment will be given to each adult with an intellectual disability in the intervention arm to recompense them for their time spent on completing the research measures at each of the three time points (not the intervention itself). Similarly, a £10 payment will be given to each adult with an intellectual disability in the control arm to recompense them for their time spent on completing the research measures at each of the three time points — baseline, 6 months post intervention, and 12 months post intervention.

### Process evaluation

The process evaluation will examine four key aspects of the feasibility of conducting a definitive trial of the Matilda intervention: (1) intervention recruitment, adherence, and reach, (2) intervention implementation, (3) intervention mechanisms, including receipt and acceptability, and (4) the feasibility of implementing Matilda within a definitive randomised trial [46]. This will employ a convergent mixed methods approach:Recruitment, matching, adherence (how often the adults with an intellectual disability and mentors meet weekly over the 6 months) and reach will be recorded by the mentors using the weekly logs. This will be further explored during the focus groups with the participants in the process evaluation.Intervention implementation and modifications will be recorded through the focus groups with the mentors exploring their engagement with the adults with an intellectual disability and key influences on implementation (perceptions of the relationship; barriers/enablers to implementation).Intervention mechanisms, receipt and acceptability needed (incl. benefits and/or adverse effects or unintended consequences) will be recorded through the focus groups with all participants, as well as with the disability staff and Volunteer Co-ordinators. We will explore recruitment, acceptability of randomisation, appropriateness of the outcome measures, acceptability, and engagement of the adults with an intellectual disability and mentors in the groups, and reasons for not engaging/dropout.

The above data (on recruitment, intervention implementation, and intervention mechanisms) will help inform the assessment of the feasibility of implementing and willingness to participate in a later definitive randomised trial.

We will also conduct a process evaluation using the Normalisation Process Theory to identify any solutions and challenges in implementing the MATILDA intervention in local community groups. We will hold focus groups with staff to support the adults with an intellectual disability who engage in the community groups, and the mentors and managers of the community groups in both sites exploring the facilitating factors and barriers to the adoption of the Matilda intervention.

Increasingly, qualitative, or mixed methods are being used in process evaluations of feasibility studies to capture salient information to inform a future randomised trial [46]. Quantitative methods will be used to assess recruitment rates, the numbers of adults with an intellectual disability and mentors matched, mentors’ weekly logs and fidelity checks. The dosage and intensity of the persons’ engagement with their local community group will also be analysed as part of the progression criteria.

### Process evaluation methodology

O’Cathain et al. [47, 48] identified four key areas that qualitative research can explore in a feasibility study: intervention, processes, outcomes, and measures. Their guidelines consist of 16 items within five domains: research questions, data collection, analysis, teamwork, and reporting. We will collect data on these five domains using focus groups involving 20 older adults with an intellectual disability (10 from Northern Ireland and 10 from London), their carers and mentors. We will explore the feasibility outcomes (recruitment, trial procedures, randomisation, mentors’ training, and supervision) and clinical outcomes (acceptability of measures, benefits, and challenges with delivering the Matilda project) and what needs modifying. We will ask some questions to the participants during the focus groups to determine how satisfied they were with the Matilda intervention and whether they would recommend it to a friend. We will also ask some questions about the appropriateness of the outcome measures, the ease of completion, and the time taken to complete them.

All participants will be invited to participate in the process evaluation. We will hold two focus groups of 6 to 8 adults with an intellectual disability who participated in the Matilda intervention in Northern Ireland and another focus group in London. There will be six focus groups in total with mentors, disability staff, and the managers of the local community groups in both sites. In addition, we will hold two focus groups with family/paid carers who participated in the Matilda intervention in both sites.

### Fidelity of intervention

We will collect information in the screening logs on how many eligible adults with an intellectual disability were randomised or the reasons for exclusion of those who were assessed for eligibility.

A checklist will be further developed to explore the fidelity of the Matilda intervention in greater detail in the process evaluation. In assessing the external validity, the extent of true collaboration in each local community group initiative will be assessed with the adults with an intellectual disability, carers, and mentors. To determine whether the Matilda intervention will be delivered as intended (adherence), each mentor will be asked to complete their own weekly paper checklist, which details attendance, frequency, activities, adverse events, etc.

We will measure the frequency of the delivery of the Matilda intervention monthly through the logs, process evaluation, and acknowledge the variability of the groups. Where possible, all the adults with an intellectual disability allocated to the intervention arm will be afforded the opportunity to access a group for the full 6-months. There may be occasions where some adults with an intellectual disability do not access their group, and this will be explored and recorded.

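### The stated routes for recording adverse events favour the Matilda arm, so events from them cannot support a between-arm statement about harms

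*Protocol article*

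**What the plan says.** The objectives in the protocol article (Aim and objectives of study) include recording adverse events and unintended consequences of the Matilda intervention. Two routes are then named.

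- **Mentor checklist** (Fidelity of intervention): "each mentor will be asked to complete their own weekly paper checklist, which details attendance, frequency, activities, adverse events, etc". It is introduced as a way of judging whether the intervention is delivered as intended.
- **Focus groups** (Process evaluation): adverse effects and unintended consequences "will be recorded through the focus groups with all participants, as well as with the disability staff and Volunteer Co-ordinators".

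On who joins the focus groups, Process evaluation methodology first says "All participants will be invited to participate in the process evaluation". It then specifies "two focus groups of 6 to 8 adults with an intellectual disability who participated in the Matilda intervention in Northern Ireland", another such group in London, and "two focus groups with family/paid carers who participated in the Matilda intervention in both sites". It lists no group for control participants or their carers.

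The control arm is described under Control or comparator group: "Those in the control group will receive usual care and will be offered three group recreational activities". Its participants complete instruments at baseline, 6 and 12 months. No mentor is part of that arm.

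**The concern.** Harms are recorded alongside intervention delivery rather than alongside trial follow-up. In a randomised trial, the control arm's main use for safety is to supply a background event rate. Older adults with an intellectual disability will have falls, illnesses and periods of distress whether or not they join a community group. If one arm is asked about events every week and the other is not asked in the same way, the recorded difference mixes the effect of the intervention with the effect of being asked.

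Three uses of the data are at stake: any later statement that Matilda does or does not cause harm, the picture available to the independent monitoring committee, and the planning of harms collection for a definitive trial.

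**Working it through.** No figure in the article bears on this point, so the first step sets the statements side by side. The second is an illustration with assumed values.

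**Step 1. Which arm each source can reach**

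| Source (section) | Matilda | Control |
|---|---|---|
| Mentors' weekly checklist (Fidelity of intervention) | Yes; about 26 weekly occasions over 6 months (52/2) | No; there are no mentors |
| Focus groups (Process evaluation) | Yes | Yes, if all participants is read literally |
| Adult and carer focus groups as specified (Process evaluation methodology) | Yes | None listed |
| Service-use inventory (Secondary outcome measures for adults with intellectual disability; Health economics evaluation) | Yes | Yes, but described as resource use, not as adverse-event recording |

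The second and third rows conflict. Even on the generous reading, the focus groups involve 20 older adults out of 64 (20/64 = 31%) and are analysed thematically. They cannot supply event counts for the control arm.

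One further feature adds to the asymmetry. Each mentor keeps a separate checklist and a participant may have one or two mentors (Matching section), so one event can be logged twice.

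**Step 2. What unequal capture would do**

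Inputs from the article: 64 participants allocated 1:1, so 32 per arm.

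Assumed inputs, not in the article: true risk p of 10% to 30%, equal in both arms; capture of 90% in Matilda (c_M); capture of 50% or 25% in control (c_C).

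- Expected participants with a recorded event = 32 × p × c
- Observed ratio = (p × c_M)/(p × c_C) = c_M/c_C
- Observed difference = p × (c_M − c_C)

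| p | c_C | Matilda | Control | Ratio | Difference |
|---|---|---|---|---|---|
| 10% | 50% | 32 × 0.10 × 0.90 = 2.9 | 32 × 0.10 × 0.50 = 1.6 | 1.8 | 4 points |
| 30% | 50% | 32 × 0.30 × 0.90 = 8.6 | 32 × 0.30 × 0.50 = 4.8 | 1.8 | 12 points |
| 10% | 25% | 2.9 | 32 × 0.10 × 0.25 = 0.8 | 3.6 | 6.5 points |
| 30% | 25% | 8.6 | 32 × 0.30 × 0.25 = 2.4 | 3.6 | 19.5 points |

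With equal capture the ratio is 1.0 and the difference is 0. The true risk cancels from the ratio, so the ratio only restates the two assumed capture rates. It shows how the distortion works and does not estimate it.

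**The case against.** The strongest reply is that the article plans no between-arm comparison of harms. Its objective concerns consequences of the Matilda intervention, and the quantitative analysis section does not mention harms. This stands. A reader might infer that the plan contains a biased safety comparison, but the text does not support that. The bias arises only if the events are later compared or attributed.

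A reader might also infer that controls have no route at all. That too is stronger than the text allows. The Process evaluation section refers to all participants, all are invited, and the service-use inventory, which covers accident and emergency and inpatient care, is not restricted by arm. Anxiety and wellbeing scales are likewise listed without restriction. Some serious events and deterioration in controls would be visible there. However, none of these is described as adverse-event recording, and harms without a service contact, such as distress when a relationship ends, could escape the inventory.

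Thirdly, this is a condensed article. General adverse-event procedures may stand in the full protocol, and their absence here is not the point. The point concerns the routes the article does state.

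Lastly, 90% capture by mentors may be optimistic. Groups typically meet for 1 to 4 hours in 1 to 3 sessions a week, so mentors would not see everything. That is a fair criticism of the illustration: lower capture in Matilda would shrink the ratio. It does not make the two arms' sources alike.

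**Conclusion.** The point holds in a limited form. The stated ascertainment is asymmetric: the one structured, ongoing source exists only in the Matilda arm, and the specified adult and carer focus groups are of Matilda participants, in tension with the statements about all participants. No stated analysis is wrong. If events from these sources were compared between arms or attributed to Matilda, controls would probably be under-counted and there would be no comparable background rate. With true risks equal and capture assumed at 90% against 50% to 25%, the observed ratio would be 1.8 to 3.6. The article gives neither event rates nor capture rates, so the actual size is unknown. The change is worth making because it is cheap.

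**What to change.** 1. Ask the same short, structured adverse-event question, with the same wording and recall period, at the 6- and 12-month assessments in both arms.
2. Base any between-arm statement about harms on that source only. Report mentor-log events separately as descriptive Matilda-arm data, counting an event logged by two mentors once.
3. Trial status says recruitment finished in March 2024 and data collection was to run to June 2025. Where assessments are already complete, state that harms are described for the Matilda arm only and not compared, and carry symmetric capture into the definitive trial.
4. Reconcile Process evaluation with Process evaluation methodology on whether control participants join the focus groups.

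The cost is one form item at two existing assessments, a few minutes per participant, with no extra visits. The price in quality is 6-month recall. The assessors are also unblinded (Randomisation and assignment of interventions), so a common question equalises the opportunity to report but does not remove every difference in reporting.
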